## Abstract

**Background**: Cryptococcal meningitis is a leading cause of death in HIV-infected patients. International treatment guidelines recommend induction therapy with amphotericin B and flucytosine. This antifungal combination is most effective, but unfortunately flucytosine is expensive and unavailable where the burden of disease is greatest. Where unavailable, guidelines recommend treatment with amphotericin and fluconazole, but this is less effective, with mortality rates of 40-50%. Faster rates of clearance of yeast from cerebrospinal fluid (CSF) are associated with better outcomes - improving the potency of antifungal therapy is likely to be an effective strategy to improve survival. Tamoxifen, a selective estrogen receptor modulator used to treat breast cancer, has anti-cryptococcal activity, appearing synergistic when combined
*in vitro *with amphotericin, and fungicidal when combined with fluconazole. It is concentrated in the brain and macrophages, off-patent, cheap and widely available. We designed a randomized trial to deliver initial efficacy and safety data for tamoxifen combined with amphotericin and fluconazole.

**Method**: A phase II, open-label, randomized (1:1) controlled trial of tamoxifen (300mg/day) combined with amphotericin (1mg/kg/day) and fluconazole (800mg/day) for the first 2 weeks therapy for HIV infected or uninfected adults with cryptococcal meningitis. The study recruits at Cho Ray Hospital and the Hospital for Tropical Diseases, Ho Chi Minh City, Vietnam. The primary end point is Early Fungicidal Activity (EFA-the rate of yeast clearance from CSF), over the first two weeks of treatment. 50 patients will be recruited providing ≈80% and 90% power to detect a difference in the EFA of -0.11 or -0.13 log10CFU/ml/day, respectively.

**Discussion:** The results of the study will inform the decision to proceed to a larger trial powered to mortality. The size of effect detectable has previously been associated with reduced mortality from this devastating disease. Particular side effects of interest include QT prolongation.

**Trial registration**: Clinicaltrials.gov
NCT03112031 (11/04/2017)

## Background

Worldwide cryptococcal meningitis results in approximately 625 000 deaths each year, most occurring within 3 months of diagnosis
^1^. It is the leading cause of death in HIV patients in Asia and Africa affecting 3.2% of the HIV infected population per year
^1^. Despite improvements in access to HIV care, the WHO estimates that even if 80% access to HIV treatment is achieved, there will be 6.5 million AIDS deaths p.a. by 2030
^2^. Thus, CM is likely to remain a significant health burden for the foreseeable future. While cryptococcal meningitis predominantly occurs in HIV infected patients, patients with other forms of immunosuppression are also affected
^3,
4^. Furthermore, in Viet Nam we see disease in apparently immunocompetent patients (N = 30 each year at the Hospital for Tropical Diseases and Cho Ray Hospital) due to infection with
*Cryptococcus neoformans* var.
*grubii*, or, more rarely,
*C. gattii*
^5^.

There has been no major advance in the treatment of cryptococcal meningitis since the 1980’s, and the 90 day case fatality rate of cryptococcal meningitis remains unacceptably high, estimated at 55% in Asia and 70% in Africa
^1^. The mainstays of induction therapy are drugs that are over 50 years old – amphotericin B and flucytosine - although these are often poorly available where disease burden is highest
^6,
7^. While amphotericin monotherapy is undoubtedly superior to fluconazole monotherapy, amphotericin combination therapy has only recently been shown to reduce mortality when compared with amphotericin monotherapy in a randomized controlled trial in Vietnam
^8^. In this study, in Vietnamese patients receiving gold standard treatment with amphotericin and flucytosine, the death rate at 10 weeks and 6 months was 31% and 35%. This compared with 33% and 46% in patients receiving amphotericin-fluconazole induction therapy (the current WHO guideline), and was significantly better than in patients receiving prolonged amphotericin monotherapy, where the death rates were 44% and 54% respectively
^8^. A biological explanation for these better outcomes is that the amphotericin-flucytosine combination has increased sterilising power – it results in significantly more rapid clearance of yeast from cerebrospinal fluid than amphotericin monotherapy
^8^. Consistent with this, the recent multi-country trial of adjunctive dexamethasone in HIV associated cryptococcal meningitis has shown that this immune modulating treatment is associated with both reduced rates of clearance of yeast from CSF and worse clinical outcomes
^9^.

Therefore, it seems that the rate of clearance of yeast from CSF is an important determinant of outcome from cryptococcal meningitis, and that improving the potency of antifungal therapy is likely to result in improved outcomes. Currently, flucytosine is unaffordable (costs of the most recently developed generic version are 15 000 USD/week), unavailable outside of Europe and the US, and has significant toxicities which can be difficult to manage in resource-poor settings. Therefore it is not currently a viable solution for patients where the vast burden of cryptococcal disease occurs
^10^. Instead, most patients worldwide are treated with amphotericin and fluconazole, as per WHO guidelines
^7^. There is a pressing need to develop affordable, safe and practicable antifungal treatment regimens with greater sterilising power.

### Current Treatment recommendations for CM

Successful treatment of CM depends upon effective anti-fungal therapy and successful management of complications, notably raised intracranial pressure. Antifungal treatment schedules for cryptococcal meningitis are not globally uniform but are affected by drug availability, costs and human resources. The Infectious Diseases Society of America convenes an international panel to draw up treatment guidelines, most recently published in 2010, and the WHO published guidelines aimed at management in resource-poor countries in 2011
^6,
7^. These conform closely to the IDSA guidelines. Treatment generally consists of a period of induction therapy using high dose or combination antifungal therapy (usually for 2 weeks), followed by a period of consolidation therapy of 8 weeks with fluconazole. After this time, provided the patient has responded to treatment, secondary prophylaxis using lower dose fluconazole is given to prevent disease relapse. It is generally considered safe to stop secondary prophylaxis if ARV therapy has resulted in suppression of the plasma viral load and there has been immune reconstitution with recovery of the CD4 cell count to > 100 cells/uL for at least 6 months.

Consistent with the local practices and the WHO and IDSA guidelines, in this study all patients in the control arm will receive anti-fungal therapy consisting of amphotericin B (1mg/kg/day) combined with fluconazole 800mg/day for 2 weeks, followed by fluconazole 800mg/day for a further 8 weeks before switching to secondary prophylaxis
^6,
7^.

## Rationale for a trial of tamoxifen

### Current indications

Tamoxifen is an off-patent, widely available (licensed in Vietnam) and affordable selective oestrogen receptor modulator (SERM)
^11^. Its initial indication was the treatment of breast cancer. There are many thousands of patient years’ experience of its use for this disease, where it has proved to be a safe, effective, and tolerable long term therapy. In addition to its effects against breast cancer, Tamoxifen, in higher doses, also has activity against other tumours including glioblastoma multiforme (GBM), desmoid tumours, lung and prostate cancer
^12–
16^.

### Antifungal activity

In addition to its anti-cancer effects, Tamoxifen has been known to have activity against yeasts for several years, this first being identified against the model yeast
*Saccharomyces cerevisiae* in 1989, and subsequently demonstrated against
*C. albicans*
^17–
19^. In 2009 the first reports of activity against
*Cryptococcus neoformans* were described
^20^. The antifungal activity is of particular interest for the following reasons:

1. 
*In vitro*, the combination of Tamoxifen with amphotericin is
**synergistic**. This contrasts with the current most effective antifungal therapy – amphotericin and flucytosine – where the effects of each drug are simply additive
^11^. A synergistic antifungal combination offers the opportunity to significantly improve CSF sterilisation and survival.2. In the mouse model of cryptococcosis, the combination of Tamoxifen with fluconazole is
**fungicidal**
^11,
21^. No other antifungal drug clearly has a fungicidal effect
*in vivo*. The lack of fungicidal effect of conventional antifungal therapies may in part explain the slow cerebrospinal fluid (CSF) sterilisation and high death rates seen in cryptococcal disease.3. Tamoxifen is
**concentrated in brain tissue**
^22,
23^. This is the main site of cryptococcal disease. Current antifungal drugs result in relatively rapid sterilisation of blood. However, they are much less effective at sterilising the central nervous system, with only approximately 50% of patients having sterile cerebrospinal fluid after 2 weeks of conventional treatment
^8^.4. Tamoxifen is
**concentrated in the macrophage phagosome**
^11^. In cryptococcal meningitis, yeast cells are engulfed by macrophages, but can survive and even reproduce within them. Unlike Tamoxifen, conventional antifungal drugs cannot penetrate the macrophage phagosome, and this therefore represents a site where yeast cells may be relatively protected from treatment.

A drug combination with both fungicidal and synergistic activity, that is concentrated in the central nervous system and within macrophages, is an exciting prospect for cryptococcal disease, and has the potential to significantly improve outcomes.

### Data from Vietnam

*In vitro* and
*in vivo* experimental data concerning the efficacy of Tamoxifen have been derived from experiments using the
*C. neoformans* type strain H99. The Minimum Inhibitory Concentration (MIC) of Tamoxifen for H99 is 8-16ug/ml. To ensure applicability in Vietnam, we have determined the MIC of Tamoxifen for 30 clinical isolates of
*C. neoformans* and
*C. gattii f*rom Vietnamese patients with cryptococcal meningitis and confirmed it to be between 2-16ug/ml (
*unpublished data*). We have also demonstrated that synergy with amphotericin B
*in vitro* is seen for the majority of strains tested. Subsequently we have performed 3D chequerboard testing of the triple combination of amphotericin with fluconazole and Tamoxifen, and have shown that there is also synergy between the 3 drugs in triple combination, and moreover that a synergistic interaction is also present for the few strains in which we failed to demonstrate synergy with the 2 drug combination. We have also demonstrated that there is no synergistic interaction
*in vitro* when Tamoxifen is combined with flucytosine.

### Mechanism of action

Tamoxifen is a selective estrogen modulating drug (SERM) that has both pro- and anti-estrogen effects. In breast cancer, it inhibits growth of (cancerous) breast tissue through modulating the expression of estrogen dependent genes and the subsequent expression of growth promoting signals. In
*Cryptococcus*, Tamoxifen binds to calmodulin and calmodulin-like protein, preventing the activation of calcineurin
^11,
20^. The calmodulin-calcineurin pathway is key in intra-cellular signalling and in controlling the response of
*Cryptococcus* to stress, such as that encountered following phagocytosis by macrophages.

### Pharmacology and dosing

Tamoxifen has excellent dose-independent oral bioavailability (approximately 100%) with minimal first-pass metabolism
^24^. The half-life is 5–7 days. Tamoxifen’s SERM activity requires serum concentrations ~100 ng/mL. This is achieved with doses of 20 – 60 mg/day, and for breast cancer treatment at this dose is recommended for 5–10 years
^25^. At these doses, brain tissue concentrations are 40-100-fold higher (4-10 µg/mL), than in serum
^23^. Higher doses of 240 – 500mg/day have been studied in clinical trials of treatment for CNS tumours, desmoid tumours and lung cancer and are well tolerated, safely achieving serum concentrations of 2-8ug/mL
^12–
14,
26–
28^. Treatment administration regimens at these doses vary: month-long cycles of 300mg/day are given for desmoid tumours in children
^28^; doses of 120mg/m
^2^ BID have been given for up to 1 year and well tolerated in patients with glioblastoma multiforme
^27^. Such treatment regimens establish Tamoxifen serum concentrations around the
*C. neoformans* MIC and, will achieve brain concentrations 40-100-fold higher, suggesting levels sufficient to treat CM will be achieved using oral dosing in humans
^23^. Moreover, uniquely compared with other antifungal drugs, Tamoxifen is further concentrated in macrophage phagosomes – an important site of
*C. neoformans* replication
^11^.

### Adverse effects

Tamoxifen is a well-tolerated drug. Adverse effects must be considered in the context of the severity of the disease being treated. Survival rates for breast cancer, GBM and cryptococcal meningitis are illustrated in
Table 1. The beneficial effects of Tamoxifen in women diagnosed with breast cancer are considered to considerably outweigh the potential adverse effects of Tamoxifen.

**Table 1. T1:** Survival rates: breast cancer, glioblastoma and cryptococcal meningitis.

Condition	Survival Metric	Survival rate *	Tamoxifen dose used
Breast Cancer	1 year survival	95%	20–40mg/day
Glioblastoma multiforme	2 year survival rate	66%	300mg/day
Small cell lung cancer	5 year survival rate	8 – 31%	300–500mg/day
Cryptococcal meningitis	6 month survival rate	45 – 55%	Suggested 300mg/day

*Sources:
http://www.cancerresearchuk.org/about-cancer/type, American Cancer Society, Beardsley
*et al.*, NEJM 2014, Park
*et al*., 2009. Note, survival rates are overall survival rates for the condition stated, and not specifically for Tamoxifen containing regimens.

## Headaches, nausea and vomiting

Data from randomised controlled trials suggest that these symptoms are no more common than in patients receiving placebo
^29^.

## Hot flushes and impaired libido

These symptoms are likely mediated through oestrogen modulation, can occur acutely, and are reversible when treatment stops.

## Pulmonary embolism, cataracts and endometrial cancer

Data from trials of prophylactic treatment for breast cancer suggest that long term use is associated with an increased risk of pulmonary embolism (Relative Risk (RR) = 3.01, 95% Confidence Interval (CI): 1.15 to 9.27), cataracts (RR = 1.13, 95% CI: 1.00 to 1.28)and endometrial cancer (RR = 2.48, 95% CI: 1.27 to 4.92,
^30^. However, the actual rate of these events is very low (0.75 per 1000 patient years, 25 per 1000 patient years and 2.2 per 1000 patient years respectively)
^29,
30^. Thromboembolic events occurred an average of 19 months after starting treatment, and none within the first 2 months
^30^. The risk of these events with short course treatment is much lower. It is not considered worthwhile to screen for factor V Leiden prior to treatment with Tamoxifen unless there is a family or personal history of previous thromboembolic disease. The increased risk of endometrial cancer is likely due to chronic modulation of oestrogen, is related to duration of use, and clearly does not exist for male patients.

## Teratogenicity

Tamoxifen is teratogenic and should not be taken by pregnant women. Fluconazole is also a teratogenic drug, and pregnant women are not eligible to enter this study. Women of child-bearing potential will be screened at study entry for pregnancy with a urine pregnancy test. All study participants will be advised to use barrier contraception until at least 3 months after study end.

## Prolongation of the QT interval

Tamoxifen can result in prolongation of the QT interval of cardiac depolarisation
^16,
31^. QT prolongation is a recognised side effect of a number of drugs including some antimicrobials, anti-arrhythmic drugs and psychoactive drugs
^32^. For some drugs, QT prolongation is associated with a risk of developing ventricular arrhythmias, particularly Torsades de Pointes (TdP). While this is a rare event, if it occurs, TdP can be life-threatening. However, not all drugs that prolong the QT increase this risk – some drugs that prolong the QT actually have anti-arrhythmic effects. Whether a drug increases the risk of TdP or not is believed to be determined by the mechanism of inhibition of ventricular repolarisation, and the duration of prolongation of the QT interval. TdP is treated with removal of the stimulus, intravenous magnesium, correction of electrolyte abnormalities, and DC cardioversion or overdrive pacing.

The mechanism of QT interval prolongation varies with different drugs and can be due to modulation of single or multiple currents involved in cardiac depolarisation
^32,
33^. Data suggest that modulation of a single current may be more likely to result in arrhythmias than QT prolongation due to modulation of multiple currents/channels
^34^. The mechanism of QT prolongation with Tamoxifen in humans is unknown. In animals there is evidence that the block is multi-channel, due to both inhibition of the I
_KR_ and I
_Ca_ channels, and may be therefore less likely to cause arrhythmia
^35–
37^. Supportive of a multichannel block mechanism for Tamoxifen is the fact that there are no case reports of TdP with Tamoxifen use, despite its extensive prescription.

Fluconazole can also result in QT prolongation. This is believed to be mediated through modulation of the I
_KR_ current of the cardiac depolarisation cycle, but data are lacking concerning whether there are also effects on other currents
^38^. TdP has been reported in patients receiving fluconazole, although again, this is a rare event
^39,
40^.

The effect of combining drugs that prolong the QT may depend upon the total number of mechanisms through which the QT is prolonged, and combining such drugs will not necessarily increase the risk of TdP
^41,
42^. In this study, to mitigate any risk of prolonged QT, all patients will have meticulous monitoring and correction of electrolyte disturbances including potassium, calcium and magnesium, and twice daily ECG monitoring. The QT interval will be manually determined by measuring the interval in 3 limb and 3 chest leads, and determining the median (machine derived estimates of the QT interval are unreliable)
^43^. The use of manual estimate of the QT has been shown to have similar performance to high resolution holter ECG monitoring
^43^. Management of QTc prolongation will be in line with the recommendations of the American Heart Association
^32^. The QT interval will be corrected (QTc) for rate using the Framingham formula. Where the QTc is found to be >500ms, the status of the patients K, Ca and Mg levels will be reviewed, corrected if necessary, and the ECG repeated before the next dose of Tamoxifen is due. If the QTc remains >500ms, the next due dose of Tamoxifen will be omitted until it is less than 500ms. When the QTc is less than 500ms, Tamoxifen will be restarted.

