### Intervention arm: Induction phase treatment (days 1–14)

Tamoxifen will be given orally in a dose of 300mg/day for the first 14 days following randomization. It will be administered by nasogastric tube where patients are unconscious. In addition patients will receive amphotericin 1mg/kg once daily i.v. and fluconazole 800mg once daily orally. The Tamoxifen will be administered in the morning combined with amphotericin and fluconazole dose.

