### Electrolyte disturbances and raised creatinine

Electrolyte disturbances are common in cryptococcal disease, usually precipitated by amphotericin treatment. The likelihood of such disturbances are mitigated by pre-emptive electrolyte replacement, sodium loading, and ensuring adequate hydration. It is routine practice to administer 2 litres of normal saline and 80mmol/L of potassium chloride daily to patients receiving amphotericin treatment. All patients in the study will receive such pre-emptive fluid and electrolyte replacement unless they are fluid overloaded or have elevated serum potassium concentrations. In the event of the serum creatinine being greater than 300umol/L, the next amphotericin dose will be missed, and the hydration status of the patient re-assessed and corrected. Amphotericin will be restarted when the serum creatinine is <200umol/L.

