1. Do not administer further tamoxifen until the QTc is ≤ 500ms.2. Immediately recheck blood potassium, calcium and magnesium levels.3. Complete a Cardiac Adverse Event form from the CRF4. Correct abnormal electrolytes into the mid normal range with intravenous supplementation (potassium chloride, calcium gluconate or chloride, and magnesium sulfate). Use intravenous access separate to the amphotericin infusion when administering electrolytes.5. Repeat the ECG, a 30 second rhythm strip, and serum electrolytes 2 hours prior to the next due dose of Tamoxifen.a) If the QTc is >500ms, the due dose of tamoxifen should be omitted.b) If the QTc is ≤500ms but there are extra-systoles, the next dose of tamoxifen should be omittedc) If the QTc is ≤500ms and there are grade 2 or greater abnormalities in serum potassium, magnesium or calcium levels, the next dose of tamoxifen should be omitted.d)If the QTc is ≤500ms, and there are no extra-sytoles, and the calcium, potassium and magnesium levels are normal or no more than grade 1 abnormal, the next due dose of tamoxifen can be given.6. Where the QTC is >500msec, the administration of tamoxifen is suspended and the patient musta)have daily ECGs and monitoring and correction of electrolytes until the QTc is less than 500ms.b)When the QTc is <500ms, Tamoxifen can be restarted according to the guidance in 5 a-d above.7. Tamoxifen is administered until day 15 after randomization. All due, received and missed drug doses must be recorded in the study case record form (CRF).8. Any patient where the QTc is greater than 500ms AND is accompanied by syncope OR arrhythmia should have review by a cardiologist.

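### The protocol gives two different conditions, and two different thresholds, for resuming tamoxifen after a QTc above 500 ms

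*Protocol article*

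**What the plan says.** Two sections of the protocol article tell staff what to do after a QTc above 500 ms.

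- *Prolongation of the QT interval* (in the rationale part). Potassium, calcium and magnesium are reviewed and corrected if necessary, and the ECG is repeated before the next dose. The dose is omitted while the QTc stays above 500 ms. Then: "When the QTc is less than 500ms, Tamoxifen will be restarted".
- *Prolonged QTc* (in the part on managing cardiac adverse events). This is a numbered procedure.
  - Step 1: "Do not administer further tamoxifen until the QTc is ≤ 500ms".
  - Step 5b: "If the QTc is ≤500ms but there are extra-systoles, the next dose of tamoxifen should be" omitted.
  - Step 5c covers a QTc at or below 500 ms where "there are grade 2 or greater abnormalities in serum potassium, magnesium or calcium levels, the next dose of tamoxifen should be omitted".
  - Step 5d allows the dose only when neither finding is present.
  - Step 6b: "When the QTc is <500ms, Tamoxifen can be restarted according to the guidance in 5 a-d above".

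*Indications for stopping Tamoxifen* refers the reader to the *Prolonged QTc* subsection for handling study drug when the QTc exceeds 500 ms. It does not say that the other section is superseded.

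Two related statements:

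- **Last dosing day.** The intervention-arm section says "Tamoxifen will be given orally in a dose of 300mg/day for the first 14 days following randomization", and the Table 2 footnote gives day 1 to day 14. Step 7 of *Prolonged QTc* says "Tamoxifen is administered until day 15 after randomization".
- **Potassium.** *Electrolyte disturbances and raised creatinine* says "It is routine practice to administer 2 litres of normal saline and 80mmol/L of potassium chloride daily".

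**The concern.** A hold-and-restart rule should give one answer for any set of findings. Here the first section makes the QTc the only condition for restarting, while the second adds rhythm and electrolyte conditions that can still block the dose. The two sections therefore give opposite instructions for a patient whose QTc has come down but who still has extra-systoles or a grade 2 electrolyte abnormality.

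The electrolyte case is plausible in this population: the protocol itself calls such disturbances common and attributes them mainly to amphotericin, which every patient receives.

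Two things are at stake. The first is uniform handling of study drug across the wards of two hospitals, in the situation the cardiac plan was written for. The second is interpretation: without a single rule, an omitted or given dose cannot be classed as following the protocol or departing from it.

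**Working it through.** No sample-size or power figure enters this point. The check is a comparison of texts, with short arithmetic for the secondary items.

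**Restart after a hold.** Each row is a possible state at the next ECG in a patient whose QTc had exceeded 500 ms.

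| State at next ECG | *Prolongation of the QT interval* | *Prolonged QTc* | Agree? |
|---|---|---|---|
| QTc above 500 ms | omit | omit (5a) | yes |
| QTc below 500 ms, no extra-systoles, electrolytes normal or grade 1 | restart | may be given (5d, 6b) | yes |
| QTc below 500 ms, extra-systoles present | restart | omit (5b) | **no** |
| QTc below 500 ms, no extra-systoles, potassium, magnesium or calcium abnormal at grade 2 or worse | restart | omit (5c) | **no** |
| QTc exactly 500 ms, no extra-systoles, electrolytes normal or grade 1 | not yet restarted | may be given under 1 and 5d; not yet under 6 | **no, and the procedure is split internally** |

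In the fourth row, the first section does ask for electrolytes to be corrected if necessary. It does not make restarting depend on the result of that correction, so the rows still differ.

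**Last dosing day.**

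- Day 15 not included, with randomization as day 1: 14 doses, 14 × 300 mg = 4,200 mg, and no conflict.
- Day 15 included: 15 doses, 15 × 300 mg = 4,500 mg. The excess is 300 / 4,200 = 7.1%.

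A day-15 dose would fall outside the twice-daily ECGs and the daily potassium checks, both of which are scheduled for the first 14 days.

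**Potassium.**

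- Unit read literally over both litres: 80 mmol/L × 2 L = 160 mmol per day.
- Per-litre read as a slip: 80 mmol per day.

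This is a twofold range from a single sentence. No other section shown gives a competing quantity.

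**The case against.** The best defence is that the two sections are a summary and a procedure, not rivals. The first closes a background account of QT risk. The second is numbered, tied to a case report form, and is the one named under *Indications for stopping Tamoxifen*. *Cardiac monitoring* sends readers back to the first section only for calculating the QTc. Within the procedure, step 6b brings in 5a to 5d, so the added conditions are consistent there. The threshold difference matters only at a reading of exactly 500 ms.

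This softens the conflict but does not remove it. The first section is written as a study instruction, saying what will be done in this trial, and nothing in the protocol ranks the two texts.

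Several stronger readings are tempting and are not supported:

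- **That the plan is unsafe.** Both sections omit the dose while the QTc remains above 500 ms. The documents show scope for non-uniform dosing, not harm.
- **That about 3 to 13 of the 25 tamoxifen patients are affected.** That range applies the protocol's expected 10–50% to 25 patients (2.5 to 12.5). It counts any QTc prolongation. The discrepant patients are those who exceed 500 ms, resolve, and still have extra-systoles or a grade 2 abnormality.
- **That the per-protocol population would change.** It excludes major violations and patients with less than one week of study drug. A fifteenth dose cannot move anyone across the one-week line, and a restart difference could do so only after a long hold.
- **That day 15 is a firm contradiction.** The wording can mean up to but not including day 15, and the continuation phase is headed days 15–70.
- **That the potassium instructions contradict each other.** There is one sentence with an ambiguous unit. The appendix on amphotericin administration is not shown and may settle it.

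**Conclusion.** The point holds for the restart rule. The two sections give opposite instructions for a patient whose QTc has fallen below 500 ms but who still has extra-systoles or a grade 2 or worse potassium, magnesium or calcium abnormality. They also use inconsistent thresholds at exactly 500 ms, including within the numbered procedure itself.

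The size cannot be quantified, because the documents give no rate for that combination of findings. The conclusion assumes only that both sections are read as instructions to staff, which their wording supports.

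The last dosing day is secondary. It is a conflict only if day 15 is read as included, and then amounts to one extra dose outside the 14-day monitoring schedule. The potassium unit is a query about one sentence. No view is taken on which rule, day or quantity is right.

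**What to change.** - **Main change.** Reconcile *Prolongation of the QT interval* with *Prolonged QTc* into one hold-and-restart rule with one threshold. State it once and replace the other text with a cross-reference. The clinical team decides which version stands.
- **Reporting.** *Trial status* says enrolment ended in May 2018 and analysis is ongoing, so new wording cannot alter ward conduct. The trial report should therefore state which rule was applied. Step 7 of *Prolonged QTc* already requires due, received and missed doses to be recorded, so each dose can be described against that rule.
- **Secondary wording.** Reconcile the day-15 statement in step 7 with days 1 to 14 in the intervention-arm section and Table 2, and report the last dosing day used. Clarify the unit of the daily potassium quantity, checking it against the amphotericin appendix.

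The cost is a correction to the text and a short statement in the report. No additional patients, visits or measurements are needed.
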